# 8.2 IDENTIFYING AEs AND SAEs

All AEs and SAEs will be recorded from the time a participant signs the consent form to take part in the study untilthe end of the study.

Participants will be asked about the occurrence of AEs/SAEs at every visit during the study. Open-ended and non-leading verbal questioning of the participant will be used to enquire about AE/SAE occurrence. Participants will also be asked if they have been admitted to hospital, had any accidents, used any new medicines or changed concomitant medication regimens.

AEs and SAEs may also be identified via information from support departments e.g. laboratories*.*

Events clearly related to a known underlying medical condition, in particular colorectal cancer, will not be recorded, including but not limited to admissions for planned or emergency surgery, admissions with bowel obstruction or admissions with rectal bleeding.

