| DESIGN | Through NHS clinical services in colorectal surgery and oncology, patients will be identified and recruited from surgical wards or surgical/oncology out-patient clinics. A sample of participants with and without a new or previous diagnosis of colorectal cancer will be included for comparison.  Participation will consist of two events in the majority of participants. Firstly a in the surgical ward or clinic lasting no longer than 20 minutes in which the research will be discussed and informed consent gained. A blood sample will be taken prior to the conclusion of recruitment and a rectal biopsy taken using a rigid sigmoidoscopy which may or may not be required as part of their routine clinical assessment. Participants will be asked to take pharmaceutical grade vitamin D tablets for 3 months. After 12 weeks of vitamin D supplementation, a final blood sample and rectal biopsy will be taken.  **If patients would like to contribute but cannot or would prefer not to take vitamin D, or cannot return for future sampling, a single sampling will be offered. This participant would undergo blood sampling and rectal biopsy as above. After this no further events would occur.** |
| AIM | To identify the underlying mechanism by which Vitamin D reduces colorectal cancer risk. |
| OBJECTIVES | To demonstrate the effects of vitamin D supplementation on serum vitamin D levels.  To demonstrate dynamic changes in gene expression in response to vitamin D.  To demonstrate the mechanism underlying the gene-environment interaction of vitamin D, susceptibility genetic variants (risk genes) and colorectal cancer. |
| OUTCOME  MEASURES | *Primary outcome:* Change in expression of genes in bowel tissue in response to vitamin D  *Secondary outcomes:*  Change in expression of genes in bowel tissue in response to vitamin D dependent on participant genotype  Change in serum vitamin D level in response to vitamin D supplementation.  Change in tissue vitamin D level in response to vitamin D supplementation. |
| ELIGIBILITY | Aged 16 years or over.  Resident of the UK. |

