# 4.2 EXCLUSION CRITERIA

The inability to provide informed consent.

Under the age of 16 years.

A non-UK resident.

Patients who may be at increased risk from rigid sigmoidoscopy:

- Individuals who are taking anti-coagulation medication.
- Individuals with platelet disease or other bleeding issues.
- Individuals with a history of a significant rectal bleed.
- Suspected or known bowel perforation
- Anal stenosis
- Acute peritonitis
- Colonic necrosis
- Toxic megacolon
- Acute severe diverticulitis
- Diverticular abscess
- Recent colonic surgery
- Anal fissure
- Severe coagulopathy
- Anticoagulant therapy
- Severe thrombocytopenia
- Severe neutropenia

**Patients who may be at increased risk from Vitamin D supplementation would not be included in the intervention arm but could still be included in the single sample arm:**

- Kidney disease
- High levels of calcium in the blood
- Atherosclerosis
- Sarcoidosis
- Histoplasmosis
- Over-active parathyroid gland (hyperparathyroidism)
- Lymphoma
- Currently taking thiazide diuretics, digoxin or other cardiac glycosides
  - Known allergy to nuts ( as peanut oil contained within vitamin D preparations)
  - Female subjects of child bearing age who are not taking effective contraception during the period of the trial

Patients in whom vitamin D levels may be unpredictable

- Individuals already established on supplementary Vitamin D.
- Individuals recently returned to the UK from an overseas holiday.
- Individuals who have recently lived abroad.
- Patients on anti-epileptic medication

Presence of any of the above exclusion criteria will be elicited from relevant patient records including clinical case notes and recent laboratory tests.

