# 5.2 RECRUITMENT OF PARTICIPANTS

Potential participants will be given a study information sheet by a member of the healthcare team either when they are on a surgical ward, or when they attend the surgical or oncology out-patients clinic for review.

They will be given appropriate time to read the information, ask questions and decide if they wish to participate. Should potential participants like more time to consider the study, they will be asked to contact the study coordinator once they have made that decision and an appointment will be made to recruit them.

The person recruiting participants will be either a member of the healthcare team or a research nurse from the dedicated research team.

Recruitment will take place in a private area or room within either the ward or clinic. The study will be discussed with participants and their questions and concerns will be addressed prior to gaining informed consent.

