# 5.5 CONCOMITANT MEDICATION

Patients currently on aspirin therapy or aspirin containing products will have this documented along with the dose and reason for prescription and any other prescribed or medicinal products being taken at the time of recruitment. Patients on already on vitamin D supplementation, or taking thiazide diuretics, digoxin or other cardiac glycosides, or anti-epileptic medication will be excluded.

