# 8. ADVERSE EVENTS

The Investigator is responsible for the detection and documentation of events meeting the criteria and definitions detailed below.

Full details of contraindications and side effects that have been reported following administration of Vitamin D can be found in the relevant Summary of Product Characteristics (SmPC).

Participants will be instructed to contact their Investigator at any time after consenting to join the trial if any symptoms develop. All adverse events (AE) that occur after joining the trial must be reported in detail in the Case Report Form (CRF) or AE form. In the case of an AE, the Investigator should initiate the appropriate treatment according to their medical judgment. Participants with AEs present at the last visit must be followed up until resolution of the event.

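### During the 12 weeks of dosing, a participant who feels well and starts a thiazide or cardiac glycoside is neither asked about it nor told to report it

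*Protocol*

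**What the plan says.** **At entry.** Section 4.2 lists, among the features that keep a person out of the intervention arm because vitamin D may carry extra risk, "Currently taking thiazide diuretics, digoxin or other cardiac glycosides". Section 5.5 repeats the exclusion. The check is made from existing material: "Presence of any of the above exclusion criteria will be elicited from relevant patient records including clinical case notes and recent laboratory tests". Section 5.5 also has staff document "any other prescribed or medicinal products being taken at the time of recruitment".

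**At visits.** Section 8.2 has staff ask about adverse events at each visit, and adds: "Participants will also be asked if they have been admitted to hospital, had any accidents, used any new medicines or changed concomitant medication regimens".

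**Between visits.** The opening text of Section 8 says: "Participants will be instructed to contact their Investigator at any time after consenting to join the trial if any symptoms develop". Section 8.2 adds that events may come to light through support departments such as laboratories. The diary in Appendix 2 records whether each day's dose was taken and nothing else.

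**Number of visits.** The design row of the study summary says: "Participation will consist of two events in the majority of participants". Figure 1 (Section 5.10) and Figure 2 (Section 5.11, the 18-week schedule) set out the two supplemented pathways.

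**The concern.** The protocol identifies a drug combination that it wants to avoid, and it writes a question that would detect it. In both supplemented schedules, however, that question is first put to a dosed participant after the last capsule, when the answer can no longer shorten exposure. The symptom-triggered instruction does not fill the gap, because someone newly prescribed a thiazide who feels well has nothing to report under it.

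Participants come from surgical wards and from surgical and oncology clinics, so a change of medicine within 12 weeks is plausible. What is at stake is participant safety during dosing. The primary outcome analysis is not affected.

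**Working it through.** No statistical calculation applies. The check sets the schedule beside the reporting rules.

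**Step 1: length of the schedules.** Figure 2 has 6 weeks without supplementation and then 12 weeks with it: 6 + 12 = 18 weeks, which matches its title. Figure 1 has the 12 dosing weeks only. Dosing therefore lasts 12 × 7 = 84 days in both.

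**Step 2: planned contacts inside those 84 days.**

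| Schedule | Contacts before the first capsule | Contacts during dosing | Next contact |
|---|---|---|---|
| Figure 1 | Baseline blood and biopsy | 0 | Return visit after 12 weeks of capsules |
| Figure 2 | Baseline, and again after the 6-week interval | 0 | Return visit after 12 weeks of capsules |

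The extra visit in Figure 2 falls before dosing, so it can pick up a medicine started in the 6-week interval but not one started later. Figure 3 (Section 5.12) is the single-sample pathway and involves no capsules.

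**Step 3: each route by which a new medicine could become known during dosing.**

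- *Entry checks (Sections 4.2 and 5.5).* These are finished before the first capsule.
- *Visit questioning (Section 8.2).* No visit falls in the window.
- *Standing instruction (Section 8).* It is triggered by symptoms, and a new prescription in someone who feels well does not trigger it.
- *Support departments (Section 8.2).* This route is incidental and concerns adverse events. A prescription is not in itself an untoward medical occurrence as defined in Section 8.1.
- *Clinically required endoscopy with a study biopsy (Section 5.6).* This could bring contact, but it is not planned.
- *Diary (Appendix 2).* It has no prompt about medicines.
- *Withdrawal (Section 4.3).* It covers the participant's own choice to leave and does not address an exclusion newly met during dosing.

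None of these is a planned route for a symptom-free change of medicine.

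**Step 4: longest delay.** A prescription at the end of dosing week *w* is first asked about 12 − *w* weeks later. For *w* = 2 that is 10 weeks. For a prescription just after the first capsule it is close to 12 weeks.

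**Step 5: dose in context.** Section 5.7 gives 3200 IU/day. Section 6.1 cites an upper limit of 4000 IU/day, and 3200 / 4000 = 80%. The protocol does not say that this limit applies to people on thiazides or cardiac glycosides.

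**The case against.** The strongest reply is that between-visit instructions to participants normally sit in the information leaflet, which is not available here. It may already ask participants to report new medicines. That stands as a limit on the practical consequence: if the leaflet says so, the remaining task is to bring Section 8 into line with it. It does not alter the rule that Section 8 itself states.

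A second reply is that the thiazide and glycoside criterion is worded for entry, and nothing in the protocol says that a later prescription requires stopping. That is fair, and it is why the remedy leaves continuation to the investigator. Even so, the reason given for the criterion is increased risk from vitamin D, and that reason does not lapse once dosing starts.

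A third reply is that the design is proportionate: a dose below the cited limit, 12 weeks only, renal function and calcium assessed at entry, and symptoms reportable at any time. Incidental contact with the clinical team is also plausible. All of this stands and keeps the point small.

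Three stronger readings are tempting, and the protocol does not support them.

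- *That every vitamin D risk in Section 4.2 can arise unnoticed.* A new diagnosis such as kidney disease or raised calcium is an adverse event under Section 8.1. It may surface through laboratories, and doubtful observations are to be recorded. Contraception is already a condition for the whole trial: "Female subjects of child bearing age who are not taking effective contraception during the period of the trial".
- *That a mid-course telephone call is needed.* That is a preference about monitoring intensity, and nothing in the protocol shows that an instruction would be insufficient.
- *That the number of participants affected, or the exposure avoided, can be calculated.* The protocol gives neither a rate of new prescriptions nor a rate of voluntary disclosure, so any such figure would be assumption throughout.

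**Conclusion.** The point holds in a narrow form. On the protocol's text, a participant who feels well and is newly prescribed a thiazide, digoxin or other cardiac glycoside during supplementation is not asked about it, and is not told to report it, until the 12 weeks of capsules are over. The firm figures are zero planned contacts in 84 days of dosing in both schedules, and a delay of up to 12 weeks.

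The conclusion assumes that Figures 1 and 2 show all planned contacts and that the leaflet adds nothing on new medicines. The first is consistent with the study summary; the second cannot be checked here. The risk is modest and its frequency unknown. This is an improvement worth considering and does not call the design into question.

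**What to change.** In the opening text of Section 8, extend the existing instruction so that participants also contact the investigator if they start or change any medicine while taking the capsules. State that the investigator then decides, with reference to the medicines named in Sections 4.2 and 5.5, whether the capsules continue. Put the same line in the participant leaflet if it is not already there.

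The cost is one clause in the protocol and, where needed, one line in the leaflet, with no added visits, samples or scheduled calls. The downside is that a participant may occasionally stop capsules before the week-12 biopsy and so contribute a shorter exposure to the primary outcome.

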**Close**

# 6. POTENTIAL RISKS AND BENFITS OF PARTICIPATION

# 6.1 POTENTIAL RISKS

Study participants may experience mild discomfort or bruising from venepuncture. Where possible, arrangements will be made to have the samples drawn at the same time as other routine samples.

Study participants may experience mild discomfort from rigid sigmoidoscopy. Rectal biopsies are routinely taken during colorectal assessment by rigid sigmoidoscopy and where possible, research samples will be taken at the same time as routine assessment. In such cases, patients recruited into the study will consent to a further additional small biopsy of rectal tissue prior to the procedure. Rigid sigmoidoscopy and rectal biopsy is not associated with significant risk of harm. Major risks include perforation, haemorrhage or pelvic sepsis, with a negligible incidence of each of these.

There is the possibility that a participant/ participant’s family will be identified as potentially having a greater risk of developing colorectal cancer and this could increase anxiety. In this instance, the lead Physician/Surgeon coordinating their care will be contacted and advised that it would be appropriate to refer the family to the local genetics service. Arrangements have been put in place with the four Scottish Regional Genetic Centres to ensure that such referrals are streamlined and that families will be seen in a timely manner.

Vitamin D is currently widely available 'over the counter' as a dietary supplement with its benefits and safety profile being well documented. The European Food Safety Authority has reported a no observed adverse effect level of up to 10000iu/day in healthy young men with minimal sun exposure with an upper limit of 4000iu/day set in order to embrace other ages and genders, including pregnant women. The following medical conditions will be elicited and relevant patients excluded from the study:

- Kidney disease
- High levels of calcium in the blood
- Atherosclerosis
- Sarcoidosis
- Histoplasmosis
- Over-active parathyroid gland (hyperparathyroidism)
- Lymphoma

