# 8.1 DEFINITIONS

An **adverse event** (AE) is any untoward medical occurrence in a study participant which does not necessarily have a causal relationship with the study intervention.

An **adverse reaction** (AR) is any untoward and unintended response to the study intervention.

A **serious adverse event** (SAE), **serious adverse reaction** (SAR). Any AE or AR that at any dose:

- results in death of the study participant;
- is life threatening*;
- requires in-patient hospitalisation^ or prolongation of existing hospitalisation;
- results in persistent or significant disability or incapacity;
- consists of a congenital anomaly or birth defect;
- results in any other significant medical event not meeting the criteria above.

*Life-threatening in the definition of an SAE or SAR refers to an event where the participant was at risk of death at the time of the event. It does not refer to an event which hypothetically might have caused death if it were more severe.

^Any hospitalisation that was planned prior to randomisation or clearly relating to a pre-existing condition will not meet SAE criteria. Any hospitalisation that is planned post randomisation will meet the SAE criteria.

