# If there is any doubt as to whether a clinical observation is an AE, the event will be recorded.

# 8.3 RECORDING AEs AND SAEs

When an AE/SAE occurs, it is the responsibility of the Investigator to review all documentation (e.g. hospital notes, laboratory and diagnostic reports) related to the event. The Investigator will then record all relevant information in the CRF and on the SAE form (if the AE meets the criteria of serious).

Information to be collected includes dose, type of event, onset date, Investigator assessment of severity and causality, date of resolution as well as treatment required, investigations needed and outcome.

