### Assessment of Causality

The Investigator will make an assessment of whether the AE/SAE is likely to be related to the study intervention according to the definitions below.

- Unrelated: where an event is not considered to be related to the study intervention.
- Possibly Related: The nature of the event, the underlying medical condition, concomitant medication or temporal relationship make it possible that the AE has a causal relationship to the study intervention. The assessment of causality will be made against the reference safety information found in the Summary of Product Characteristics [last updated 29th June 2013].

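### The adverse-event exemption in section 8.2 overlaps the biopsy harms named in section 6.1 with no exception for study procedures, and causality has only the vitamin D product information as its named reference

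*Protocol*

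**What the plan says.** Section 8 sets a general rule: "All adverse events (AE) that occur after joining the trial must be reported in detail". Section 8.2 starts from the same position, with recording from consent to the end of the study, and then withdraws a class of events: "Events clearly related to a known underlying medical condition, in particular colorectal cancer, will not be recorded". The sentence goes on to give examples, saying that such events "will not be recorded, including but not limited to admissions for planned or emergency surgery, admissions with bowel obstruction or admissions with rectal bleeding", so the list is expressly not exhaustive. The sentence printed just before section 8.3 adds: "If there is any doubt as to whether a clinical observation is an AE, the event will be recorded".

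On the procedure, section 6.1 states: "Major risks include perforation, haemorrhage or pelvic sepsis, with a negligible incidence of each of these". The Study Summary says that the biopsy may or may not be needed for routine care. It also offers a single-sample option, with blood and biopsy but no vitamin D.

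On causality, section 8.4 relates each event to the study intervention and says: "The assessment of causality will be made against the reference safety information found in the Summary of Product Characteristics". Expectedness is judged against the same SmPC. Under section 8.5, every SAE goes to ACCORD within 24 hours. Only SAEs that are both possibly related and unexpected go on to the ethics committee, and the annual report lists serious adverse reactions (SARs).

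The footnote on hospitalisation in section 8.1 says that an admission clearly due to a pre-existing condition is not an SAE, and then: "Any hospitalisation that is planned post randomisation will meet the SAE criteria".

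**The concern.** Participants are recruited from colorectal surgical wards and from surgical and oncology clinics, and some have colorectal cancer. In them, bleeding or an acute abdomen after a study biopsy can look like the disease. Section 8.2 asks for a judgement of cause before anything is written down, and its examples are the admissions most easily confused with a biopsy complication. A wrong judgement at that point leaves no record for anyone to review.

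The causality rules are written for a medicine, although the study also imposes a procedure. At stake are the completeness of the safety record for biopsies that may not be needed for care, and what the ethics committee is told about them. The incidence that section 6.1 calls negligible can be checked in this study only if complications are captured.

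**Working it through.** No arithmetic applies: the protocol gives no event rate or count on this point. The check sets the rules side by side and follows an event through them.

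**Overlap of section 6.1 with the examples in section 8.2**
- Haemorrhage could present as an admission with rectal bleeding, which is a listed example.
- Perforation could present as an admission for emergency surgery, which is a listed example.
- Pelvic sepsis matches no listed example, though the list is open.

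So up to two of the three named major risks overlap the examples. The number of study biopsies is one in Figure 3 (single sample), two in Figure 1 (12 weeks of vitamin D) and three in Figure 2 (18-week protocol).

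**An admission with bleeding after a study biopsy**
1. *Colorectal cancer, and the investigator judges the bleed clearly due to the tumour.* Section 8.2 says not to record it. It is then not assessed under 8.4 or sent to ACCORD under 8.5. The Chief Investigator's power in 8.4 to upgrade an AE has nothing to act on.
2. *Colorectal cancer, and the cause is uncertain.* The event is not clearly due to the disease, so it is recorded and, as an admission, goes to ACCORD. Its class then depends on what the study intervention is taken to be. If that is vitamin D alone, with the SmPC as reference, the event may be classed unrelated and miss both the ethics committee and the SAR list. If the biopsy is included, timing supports possibly related. The event is then unexpected against a vitamin D SmPC, and it reaches the ethics committee.
3. *No known condition that explains the bleed.* The exemption does not apply. The event is recorded, and the same fork follows as in 2.
4. *Single-sample participant.* If the study intervention means vitamin D alone, no event can be related, because none is given.

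**The doubt sentence.** It covers doubt about whether an observation is an AE. Section 8.1 defines an AE without regard to cause, so a bleeding admission is an AE whether the tumour or the biopsy caused it. Doubt about cause therefore does not literally trigger the sentence. The protection in case 2 comes from the word 'clearly' in section 8.2.

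**Surgery planned after entry for a known cancer.** The first sentence of the 8.1 footnote makes it not an SAE, because it relates to a pre-existing condition. The second makes it an SAE, because it was planned after randomisation. Section 8.2 says not to record it, while section 8 requires all AEs. Neither the design nor any of the three schedules contains a randomisation, so the time point used in 8.1 does not exist. Section 8.2 uses consent.

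**The case against.** A reader might infer three stronger things, and the protocol supports none of them.

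- *That rectal bleeding and emergency surgery admissions are never recorded.* They are examples within a class limited to events clearly due to a known condition. A bleed caused by the biopsy, or of uncertain origin, falls outside it.
- *That a biopsy injury has no route to possibly related.* The definition in section 8.4 also weighs the nature of the event, the underlying condition, other medication and timing, and nothing expressly limits the study intervention to vitamin D.
- *That such events go unreported.* Every recorded SAE reaches ACCORD whatever its cause. For recorded events the gap is only at the ethics committee and in the SAR list.

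It can also be said that exposure is limited. Section 6.1 calls the incidence negligible. Section 4.2 excludes people on anticoagulants, with bleeding problems, with a history of significant rectal bleeding or with recent colonic surgery. Some participants have no colorectal cancer, and some biopsies are taken during routine assessment. Part of the 8.1 footnote agrees with 8.2, and its mention of randomisation is a drafting slip separate from biopsy harms.

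All of this stands, and it lowers the severity. It does not remove the gap: the exemption still depends on one person's judgement made before recording, with no exception for study procedures, and the only named reference is for a product that some participants never take.

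**Conclusion.** The point holds as a gap in safety capture and classification. Two routes to loss follow from the text: a biopsy complication attributed to known disease and never recorded, and a recorded one classed unrelated and so absent from ethics committee reporting and the SAR list. The first concerns participants with a known condition that could explain the event; the second could arise in any participant, and most plainly in the single-sample group. Separately, sections 8, 8.1 and 8.2 conflict on surgery planned after entry, and 8.1 relies on a randomisation that this study does not have.

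The conclusion assumes that investigators follow the text as written and that no other study document defines the study intervention to include the biopsy. The size cannot be put as a number of events. The primary outcome and sample size are untouched. The amendment is worth making, but this is not a must-fix defect.

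**What to change.** - **Section 8.2:** state that the exemption does not apply to any event possibly related to a study sigmoidoscopy or biopsy.
- **Sections 8.1 and 8.4:** state that study procedures count as study intervention. Assess causality separately for the procedure and for vitamin D, with the procedure assessment not limited to the SmPC.
- **Expectedness:** do not use the risk list in section 6.1 to class serious procedural harms as expected. Under section 8.5 that would remove them from expedited reporting to the ethics committee.
- **Section 8.1:** replace randomisation by consent, in line with section 8.2.
- **Sections 8, 8.1 and 8.2:** reconcile them so that surgery planned after entry for a known condition has one stated status.

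The cost is a wording amendment, one extra causality field on the AE form and a few more recorded events.
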